### Outcomes

The outcomes will be assessed by independent researchers who have been trained before the study. The primary outcomes are the SPPB score and 6-month all-cause rehospitalization. The secondary outcomes include cardio-pulmonary function, activities of daily living (ADL), in-hospital mortality rate and 6-month all-cause mortality rate. Cardiac function indicators are as follow: 6-min walking test (6 MWT) before discharge, SV before discharge, EDFR, SVR, NYHA classification, biochemical markers of myocardial necrosis, N-terminal brain natriuretic peptide (NT-pro BNP), and left ventricular ejection fraction (LVEF). Pulmonary function indicators include 1 second rate of transfer/discharge (FEV1/FVC) and maximum ventilation volume per minute (MVV). In addition, we will evaluate the Short-Form 36-Item Health Survey (SF-36), psychological assessment, nutritional assessment and cardio-cerebrovascular events (Table 2).

**Table 2 T2:** The follow-up schedule.

	**Baseline**	**1 month**	**3 months**	**6 months**
Smoking	X			
Sports	X			
Participate in phase II cardiac rehabilitation				
Psychological assessment	X		X	X
Nutritional assessment	X	X		X
Rehospitalization				
Cardio-cerebrovascular events				
36-item short-form (SF-36)	X	X	X	

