### Sample Size

According to the results of the previous study, the baseline SPPB sores was 6.0 ± 2.8 in CR group and 6.1 ± 2.6 in control group, the SPPB sores at 3 months was 8.3 ± 0.2 in CR group and 6.9 ± 0.2 in control group (14). To minimize both false positive and false negative errors, the type-I error rate (α) is set at 0.01 instead of 0.05 and the type-II error rate is set at 0.1 instead of 0.2. The sample size is calculated according to the following formula: *n* = 2σ^2^ × *f* (α,β)/(μ_1_-μ_2_)^2^ (19). The sample size of each group was estimated to be 44 per group. Taking approximate a 20% drop-off rate and a 7% missing rate into account, the final sample size was set to 60 per group. Therefore, a total of 120 subjects will be recruited in this study.

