### Data Analysis

Statistical analysis will be conducted using SPSS 25.0 (IBM, Chicago, IL, USA) statistical software. *P* < 0.05 (two-sided) was considered to be statistically significant. Normally distributed continuous variables were presented as mean ± SD and evaluated with paired or unpaired Student's *t* test. Non-normally distributed continuous variables were expressed as median with interquartile range (IQR) and determined by Wilcoxon signed-rank test or Mann-Whitney U test. Categorical variables were recorded as frequency and percentage (*N*, %) and performed by χ^2^ test or Fisher's exact test as appropriate.

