## Discussion

This is a study protocol for a single-center, randomized controlled, single-blind clinical trial to evaluate the efficacy and safety of phase I CR in patients hospitalized in CICU with ADHF. The results of this study will provide reliable evidence for tailored and progressive CR intervention in patients with ADHF.

CR is one of the treatment strategies for HF, which services as one way to reduce the financial burden of HF treatment (24). A recent trial showed CR could improve physical function in patients with ADHF, especially those in NYHA Class II group (14). CICU is usually needed for the patients with ADHF presented with signs of respiratory distress, hypoperfusion, and hemodynamic instability. These patients are at high risk for unexpected in-hospital mortality and re-hospitalization (25). Whether personalized, tailored, and progressive CR intervention is associated with improved QOL and outcomes in patients in CICU with ADHF has not yet been clarified. Thus, evidence on the efficacy and safety of CR intervention is needed in individuals enter the CICU with ADHF.

Tailoring exercise prescription based on the characteristics of patients is necessary for the development of CR in ADHF. Improved SPPB score was related to better prognosis in patients with HF (26). The PEARL study and the REHAB-HF trial showed CR could improve the SPPB score among elderly patients with ADHF (14, 27). However, re-hospitalization rate was not included as a study endpoint in PEARL study. In REHAB-HF trial, reduced re-hospitalization rate was not observed in CR group during the follow-up period. In addition, the majority of CR interventions were conducted in the outpatient setting in REHAB-HF trial. We hypothesize early phase I CR training will increase the SPPB score and reduce the re-hospitalization rate. Additionally, our personalized, tailored and progressive CR program include comprehensive physical fitness interventions. The physical fitness interventions include strength, flexibility, coordination, and balance training. The psychological interventions will be performed by specialized psychological intervention therapists. To achieve the outcomes, strict follow-up procedure will be conducted for 6 months. These measures could promote individualized CR intervention in patients with ADHF.

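### Two primary endpoints share one unadjusted two-sided 0.05 threshold with no success rule, in conflict with the 0.01 used for sizing, and no power is stated for rehospitalisation

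*Protocol article*

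**What the plan says.** - **Endpoints.** Outcomes states: "The primary outcomes are the SPPB score and 6-month all-cause rehospitalization". The Abstract names the same pair. The Introduction is less clear: it calls SPPB one of the primaries, then lists 6-month rehospitalisation with the outcomes to be evaluated additionally.
- **Analysis threshold.** Data Analysis gives one rule for all tests: P < "0.05 (two-sided) was considered to be statistically significant". It has no split of alpha, no order of testing and no statement on whether one or both primaries must be significant.
- **Sizing.** Sample Size says "the type-I error rate (α) is set at 0.01 instead of 0.05" and "the type-II error rate is set at 0.1 instead of 0.2", with the declared aim of limiting both kinds of error. Its only inputs are SPPB figures: "the baseline SPPB sores was 6.0 ± 2.8 in CR group and 6.1 ± 2.6 in control group", and "the SPPB sores at 3 months was 8.3 ± 0.2 in CR group and 6.9 ± 0.2 in control group". The result is: "The sample size of each group was estimated to be 44 per group". Allowance for drop-out and missing data raises this to 60 per group.
- **Rehospitalisation.** The protocol gives no control risk, target reduction or power for it. The Discussion hypothesises a benefit on both primaries, but says of the trial that supplied the SPPB figures: "In REHAB-HF trial, reduced re-hospitalization rate was not observed in CR group during the follow-up period".

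**The concern.** With two primaries and one unadjusted threshold, the trial's false-positive rate depends on a decision the protocol does not record. If a significant result on either endpoint may be presented as a positive trial, the error rate is close to twice the nominal 5%. The Sample Size section chose a stricter alpha to prevent false positives, and the analysis rule drops that protection without comment. A P value between 0.01 and 0.05 would therefore be positive under one section and not under the other.

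The second issue is what a rehospitalisation result could show. That endpoint has primary status, but nothing indicates that 120 patients suffice for it. A non-significant result would then be hard to interpret, because the protocol sets out no effect the trial was able to detect.

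**Working it through.** **1. The plan's own sample size.** Formula in Sample Size: n = 2σ² × f(α,β)/(μ₁−μ₂)². With two-sided α = 0.01 (sidedness is not stated there) and β = 0.1, f = (2.576 + 1.282)² = 14.88.
- σ = 2.8 and the within-CR change 8.3 − 6.0 = 2.3: n = 2 × 7.84 × 14.88 / 5.29 = 44.1. This matches the stated 44.
- The between-group difference 8.3 − 6.9 = 1.4: n = 102.6, 110.7 and 119.0 for σ = 2.6, 2.7 and 2.8. These do not match.
- Attrition: 44/0.73 = 60.3, or 44/(0.80 × 0.93) = 59.1. Both agree with 60.

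Only SPPB enters this calculation.

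**2. Family-wise error.** Two tests, both null hypotheses true:

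| Rule | Error |
|---|---|
| Either suffices, 0.05 each, independent | 1 − 0.95² = 9.75% |
| Either suffices, 0.05 each, correlation 0.5 | 9.07% |
| Either suffices, 0.05 each, correlation 0.7 | 8.35% |
| Either suffices, 0.05 each, upper bound | 10% |
| Either suffices, 0.01 each, independent | 1 − 0.99² = 1.99% |
| Both required, 0.05 each | at most 5% |

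**3. Power for rehospitalisation.** Control risk and effect are assumptions, because the protocol gives neither. Normal approximation for two proportions, two-sided 0.05:

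power = Φ[(|p₁ − p₂| − 1.96 × √(2p̄(1−p̄)/n)) / √((p₁(1−p₁) + p₂(1−p₂))/n)]

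Example with 40% v 30% and n = 60: (0.10 − 1.96 × 0.0871)/0.0866 = −0.816, so power is 20.7%.

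| Control risk | 25% reduction, n=60 (n=44) | 30% reduction, n=60 (n=44) | Halving, n=60 (n=44) |
|---|---|---|---|
| 30% | 15% (12%) | 20% (16%) | 50% (39%) |
| 40% | 21% (16%) | 28% (22%) | 67% (54%) |
| 50% | 28% (22%) | 38% (29%) | 82% (68%) |

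For 80% power with 60 per arm, risk must fall from 30% to 9.7%, from 40% to 17.1% or from 50% to 25.4%.

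**4. What the choice of alpha costs SPPB.** Power = Φ[1.4/(2.7 × √(2/n)) − z], taking the between-group difference of 1.4 and σ = 2.7, midway between the two baseline SDs. With n = 60 the first term is 2.84.

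| Two-sided alpha | z | n=60 | n=44 |
|---|---|---|---|
| 0.05 | 1.960 | 81% | 68% |
| 0.025 | 2.241 | 72.5% | 57.6% |
| 0.01 | 2.576 | 60% | 44% |

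**The case against.** The strongest reply is that the inflation depends on a reading the protocol never states. Its hypotheses are worded jointly, as better function and fewer rehospitalisations, and if both were required the error would not exceed 5%. A reader might infer that the false-positive rate nearly doubles as a matter of fact. The text does not support that, because it is silent on either versus both. It does not exclude the inflating reading either.

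A reader might also infer that the trial has almost no power for rehospitalisation. That cannot be derived without a control risk and a target effect. Power is low for moderate reductions but 82% for a halving from 50% with 60 per arm.

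Third, this is a condensed article and a detailed multiplicity procedure may sit in an analysis plan that is not shown. Its absence alone would be no finding. What stands is what the article itself fixes: two primaries, one unqualified 0.05 threshold, and a different alpha in Sample Size.

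Last, the protocol describes its aim as exploratory and leaves firm proof to later studies, so it should not be assumed that a null rehospitalisation result would be reported as absence of effect. That lessens the expected harm, but the endpoint still carries primary status.

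**Conclusion.** The point holds in conditional form. The protocol names two primaries, applies an unadjusted two-sided 0.05 to each without a success rule, and contradicts the 0.01 of its own Sample Size section. If either endpoint suffices, family-wise error is 9.75% under independence, somewhat less under positive correlation and never above 10%. If both are required there is no inflation.

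Sizing rests on SPPB alone and no power is stated for rehospitalisation. Under assumed control risks of 30-50% with 60 per arm, power is about 15-28% for a 25% relative reduction. A halving reaches about 80% only from a 50% control risk; from lower risks a larger proportional fall is needed.

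Nor should the sample size be described as adequate for SPPB at the stated alpha and power. The 44 per group reproduces from the within-arm change of 2.3, while the between-group difference of 1.4 needs about 103 to 119. That is a separate matter, but it limits which alpha rule is affordable.

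**What to change.** 1. Reconcile the alpha in Sample Size with the one in Data Analysis, so that one level governs both sizing and testing.
2. Pre-specify one rule that holds total two-sided error at 0.05 across the two primaries. Two suitable options:
   - **Fixed order:** test SPPB at 0.05, and test rehospitalisation confirmatorily at 0.05 only if SPPB succeeds. SPPB keeps its 81% power (60 per arm, difference 1.4, SD 2.7). The cost is that rehospitalisation cannot be claimed if SPPB fails.
   - **Holm:** test the smaller P value at 0.025 and, if it succeeds, the other at 0.05. Either endpoint can then be claimed alone. The cost is a stricter first threshold, at which SPPB power is 72.5% under the same assumptions. Hochberg is an alternative if the two test statistics can be taken as not negatively dependent.
3. State that the sample size was calculated from SPPB only, without saying that it is sufficient for SPPB. Give the rehospitalisation differences that 60 per arm could detect under stated control risks.
4. Report rehospitalisation as an estimate with a 95% CI, and draw no conclusion of no effect from a non-significant result.

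Keeping SPPB at 0.01 would also control the error, but on the same assumptions it lowers SPPB power from about 81% to 60%. The text change is a few sentences and needs to be made before outcome data are seen by arm.

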### Data Management

An EpiData database will be established based on the CRFs project. The researchers will fill in relevant information back-to-back timely and accurately. The study data will be monitored by researchers at the School of Public Health of Xiamen University every 3 months.

### Data Analysis

Statistical analysis will be conducted using SPSS 25.0 (IBM, Chicago, IL, USA) statistical software. *P* < 0.05 (two-sided) was considered to be statistically significant. Normally distributed continuous variables were presented as mean ± SD and evaluated with paired or unpaired Student's *t* test. Non-normally distributed continuous variables were expressed as median with interquartile range (IQR) and determined by Wilcoxon signed-rank test or Mann-Whitney U test. Categorical variables were recorded as frequency and percentage (*N*, %) and performed by χ^2^ test or Fisher's exact test as appropriate.

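### SPPB is sized at a type-I error of 0.01 but judged at two-sided P < 0.05, so the declared protection against a false-positive SPPB result is not delivered

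*Protocol article*

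**What the plan says.** The Sample Size section of the protocol article bases its calculation on SPPB alone. It states that "the type-I error rate (α) is set at 0.01 instead of 0.05" and that "the type-II error rate is set at 0.1 instead of 0.2", and introduces both choices with the reason "To minimize both false positive and false negative errors". From these it reports that "The sample size of each group was estimated to be 44 per group", later raised to 60.

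The Data Analysis section gives the only significance threshold for the tests themselves: P < "0.05 (two-sided) was considered to be statistically significant". It is worded for all analyses and makes no exception for SPPB. The Outcomes section names SPPB as one of two primary outcomes and says nothing about significance levels.

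**The concern.** The level that the Sample Size section names and rejects is the level that the Data Analysis section adopts. An SPPB comparison with, say, P = 0.02 would meet the analysis threshold and miss the error rate on which the trial was sized. A reader of the results could not tell from the protocol which standard had been fixed in advance, and a report could cite either. The justification given for the sample size also promises a protection against false positives that the analysis, as written, does not provide.

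**Working it through.** **Inputs**

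- Design: α = 0.01, β = 0.1, 44 per group (Sample Size).
- Analysis: two-sided 0.05 (Data Analysis).
- Baseline SPPB in the earlier study (Sample Size): mean 6.0 with SD 2.8 under CR, mean 6.1 with SD 2.6 for controls.
- Follow-up values from that study, same section: "the SPPB sores at 3 months was 8.3 ± 0.2 in CR group and 6.9 ± 0.2 in control group".
- Sidedness of the 0.01: not stated.

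**Step 1. Is 0.01 a slip, or does the stated size rest on it?**

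The protocol's formula is n = 2σ² × f(α,β)/(μ₁−μ₂)², with f = (z_α + z_β)². With σ = 2.8 and a difference of 8.3 − 6.0 = 2.3:

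| α | f | n per group |
|---|---|---|
| 0.01 two-sided | (2.576 + 1.282)² = 14.88 | 2 × 7.84 × 14.88 / 5.29 = 44.1 |
| 0.01 one-sided | (2.326 + 1.282)² = 13.02 | 2 × 7.84 × 13.02 / 5.29 = 38.6 |
| 0.05 two-sided | (1.960 + 1.282)² = 10.51 | 2 × 7.84 × 10.51 / 5.29 = 31.1, so 32 |

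Two-sided 0.01 returns the stated 44 (45 if always rounded up). Inflation also agrees: 44 / 0.80 / 0.93 = 59.1, hence 60. The article does not say which difference and SD were used, so this is the closest reconstruction, not proof. A one-sided 0.01 with a difference of 2.2 and SD 2.8 gives 42.2, which is near but not as close. One-sided 0.05 with 80% power also lands near 44 for differences of 1.4 to 1.5, but contradicts both the stated α and the stated power.

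**Step 2. Size of the discrepancy for the SPPB test**

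- If 0.01 is two-sided: 0.05 / 0.01 = 5.
- If 0.01 is one-sided, it equals 0.02 two-sided: 0.05 / 0.02 = 2.5.

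**Step 3. Which observed results fall between the two levels?**

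With 44 per group and SD 2.8, the standard error of the difference is 2.8 × √(2/44) = 0.597, on 86 degrees of freedom.

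- Two-sided 0.05: 1.988 × 0.597 = 1.19 points.
- Two-sided 0.01: 2.634 × 0.597 = 1.57 points.

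The between-group difference at 3 months in the earlier study is 8.3 − 6.9 = 1.4 points, inside this band. There t = 1.4 / 0.597 = 2.35, and P is about 0.02. With SD 2.6 the standard error is 0.554 and the band is 1.10 to 1.46, which still contains 1.4.

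**Step 4. What each choice of level means for power**

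On the inputs that reproduce 44 (difference 2.3, SD 2.8, 44 per group), the standardised shift is 2.3 / 0.597 = 3.853.

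| Level (two-sided) | Normal approximation | Noncentral t |
|---|---|---|
| 0.01 | Φ(3.853 − 2.576) = 89.9% | 88.5% |
| 0.05 | Φ(3.853 − 1.960) = 97.1% | 96.8% |

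**The case against.** The strongest reply is that the Data Analysis section holds the only explicit decision rule, and that the α in the Sample Size section is merely a planning input. A trial sized at a stricter level than it tests at is not invalid: it tests at a conventional level with more power than planned. That is right as far as it goes, and testing SPPB at 0.05 is not in itself an error. But α is not presented as a mere planning margin. It is described as the type-I error rate and justified by the wish to avoid false positives, and a sample size cannot do that on its own. Only the threshold applied to the data sets the false-positive rate. The contradiction survives.

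A reader might also be tempted to infer more than the documents support:

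- **That the false-positive rate of the whole trial is five times the declared one.** The 0.01 is attached to a calculation on SPPB only. The factor applies to that one test, and it is 2.5 if 0.01 was meant as one-sided.
- **That the threshold will be picked after the data are seen.** The text leaves that open, but nothing in it shows such an intention.
- **That the mismatch leaves the trial badly underpowered.** With a difference of 1.4, SD 2.8 and 44 per group, power is about 39% at 0.01 and 64% at 0.05. Those figures are low because 1.4 is used in place of the 2.3 that reproduces 44. That is a separate question about the effect size, not a consequence of having two significance levels.

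**Conclusion.** The point holds for SPPB and is wrong as written. The declared type-I error is 1% and the one that the analysis will deliver is 5%: five times as high if 0.01 is two-sided, and 2.5 times if one-sided. Two-sided is the only sidedness that the article states anywhere, and two-sided 0.01 gives the closest reproduction of 44 per group, so five is the likelier figure. Results with P between 0.01 and 0.05 have no unambiguous status. Under the assumptions of 44 evaluable patients per group and an SD of 2.8, these are observed differences of about 1.19 to 1.57 points, a range that takes in the earlier study's own result. An unseen analysis plan does not remove the problem, because the article states both levels and such a plan could follow one only by departing from the other. How error should be shared between the two primary outcomes is a separate multiplicity question, which this point does not settle.

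**What to change.** Before unblinding, state one significance level for SPPB, with its sidedness, in both sections. Either option removes the contradiction:

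1. **Keep 0.01.** Amend Data Analysis so that SPPB is judged at two-sided 0.01, as in the sample-size calculation. The cost is a stricter threshold and lower power than at 0.05: about 89% against 97% on the inputs that reproduce 44.
2. **Keep 0.05.** Delete the 0.01 claim and its false-positive rationale from Sample Size, and restate power at two-sided 0.05 with the difference and SD used. The cost is giving up the stricter error control that the article now advertises.

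Each is a short text amendment. Neither requires a change to recruitment, conduct or data collection. Made after the results are known, the same amendment would not be credible.

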## Materials and Methods

### Study Design

This is a single-center, randomized controlled, single-blind clinical trial, which is designed to evaluate the efficacy and safety of CR in patients hospitalized in CICU with ADHF. This study protocol follows the principles of the Standard Protocol Items: Recommendations for Intervention Trials (SPIRIT) statement (18). This study has been approved by the Ethics Committee of Xiamen Cardiovascular Hospital of Xiamen University (approved number: 2021YLK6) and registered at Chinese Clinical Trial Registry (registration number: ChiCTR2100050151).

This study includes a 5-day intervention period and a 6-month follow-up period. A total of 120 patients hospitalized in CICU with ADHF will be randomly assigned to the two groups with a 1:1 ratio. Participants will receive tailored and progressive CR intervention or attention control. Clinical outcome evaluation will be conducted before and after intervention and at 6 months. The flow diagram of the study protocol is outlined in Figure 1.

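### The only tests named for continuous outcomes, which include the primary SPPB score, are unadjusted or within-arm; a baseline-adjusted between-arm model would be more precise, by an amount that depends on an unstated correlation

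*Protocol article*

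**What the plan says.** The Outcomes section of the protocol article states: "The primary outcomes are the SPPB score and 6-month all-cause rehospitalization". SPPB is summarised by mean and ± throughout the Sample Size section, so it falls under the rule for continuous variables in Data Analysis.

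That rule has two branches. For normal data: "Normally distributed continuous variables were presented as mean ± SD and evaluated with paired or unpaired" Student's t tests. For non-normal data, the comparison is "determined by Wilcoxon signed-rank test or Mann-Whitney U test". No covariate-adjusted method for a continuous outcome appears anywhere in the article, and Data Analysis does not say which of the four tests is the primary SPPB comparison. The significance level there is two-sided 0.05.

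On baseline measurement, Study Design states: "Clinical outcome evaluation will be conducted before and after intervention and at 6 months". SPPB has no row in Table 2 (the follow-up schedule), so a baseline SPPB is implied by this sentence and not listed separately.

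Sample Size cites an earlier trial in which "the baseline SPPB sores was 6.0 ± 2.8 in CR group and 6.1 ± 2.6 in control group", and "the SPPB sores at 3 months was 8.3 ± 0.2 in CR group and 6.9 ± 0.2 in control group". It then says "the type-I error rate (α) is set at 0.01 instead of 0.05" and "the type-II error rate is set at 0.1 instead of 0.2", and arrives at 44 evaluable patients per group, recruited as 60.

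**The concern.** Three features of the rule are weak for a primary outcome.

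1. An unpaired test on follow-up scores makes no use of baseline SPPB. By the protocol's own figures, baseline SPPB varies between patients with an SD of 2.6 to 2.8. If it is correlated with follow-up SPPB, part of the residual variance could be removed without extra patients.
2. A paired test compares an arm with its own past. The control arm of the cited trial gained 0.8 points (6.1 to 6.9), so a significant within-arm change says nothing about the treatment.
3. Choosing between t and rank tests by apparent normality lets the data decide which test, and which effect measure, carries the primary result.

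At stake is mainly precision, in a trial whose power for the cited between-arm difference is already well below what it claims. There is also a risk that a within-arm p value is read as evidence of efficacy.

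**Working it through.** **Inputs.** From Sample Size: baseline SD 2.8 (CR) and 2.6 (control); follow-up means 8.3 and 6.9, a between-arm difference of 1.4; 44 evaluable per arm; alpha 0.01; power 90%. From Data Analysis: two-sided alpha 0.05. Assumed here: follow-up SD equal to baseline SD (the ±0.2 at 3 months cannot be a patient-level SD beside 2.6 to 2.8); two-sided testing at 0.01; r of 0.3, 0.5 and 0.7, since the article gives no r; and the 3-month effect carried over, since the article fixes no time point for SPPB.

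**The plan's own figure.** Its formula is n = 2σ²·f(α,β)/(μ₁−μ₂)², with f = (2.576 + 1.282)² = 14.88.
- Difference 1.4, SD 2.6: 2 × 6.76 × 14.88 / 1.96 = 102.6 per arm.
- Difference 1.4, SD 2.8: 2 × 7.84 × 14.88 / 1.96 = 119.0 per arm.
- Difference 2.3 (8.3 − 6.0, the CR arm's own change), SD 2.8: 2 × 7.84 × 14.88 / 5.29 = 44.1 per arm.

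With the stated alpha and power, 44 is matched by the within-arm change and not by the between-arm difference. The step to 60 reproduces: 44/(0.80 × 0.93) = 59.1, or 44/0.73 = 60.3.

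**Unadjusted power with 44 per arm.** SE = 2.8 × √(2/44) = 0.597; noncentrality = 1.4/0.597 = 2.35. The noncentral t on 86 df gives 39% at alpha 0.01 and 64% at 0.05.

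**Baseline-adjusted power.** The residual SD is SD × √(1−r²), and one further degree of freedom is used.

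| r | SE factor √(1−r²) | Equivalent n factor 1/(1−r²) | Power, alpha 0.01 | Power, alpha 0.05 |
|---|---|---|---|---|
| unadjusted | 1 | 1 | 39% | 64% |
| 0.3 | 0.954 | 1.10 | 43% | 68% |
| 0.5 | 0.866 | 1.33 | 53% | 76% |
| 0.7 | 0.714 | 1.96 | 74% | 90% |

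With SD 2.6 every figure is somewhat higher: 46% unadjusted, then 51%, 61% and 81% at alpha 0.01; 70%, then 75%, 82% and 94% at alpha 0.05.

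**Against a change-score t test.** The SD of change is SD × √(2(1−r)). With SD 2.8 and alpha 0.01, power is 26% at r = 0.3, 39% at r = 0.5 (the same as raw scores) and 65% at r = 0.7. At r = 0.7 the adjusted model therefore gains 9 points over change scores (65% to 74%), against 35 over raw follow-up scores (39% to 74%).

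**The paired test in the control arm.** With change 0.8, SD 2.6 and n = 44, the SD of change is 3.08, 2.60 and 2.01 for r of 0.3, 0.5 and 0.7. The chance that the control arm alone reaches p < 0.05 is 39%, 51% and 73%.

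**The case against.** The strongest reply is that Data Analysis is one generic paragraph in a condensed article. It never mentions SPPB, and a full analysis plan may name the primary model. That carries some weight: applying the rule to SPPB is an inference. But the paragraph does state a complete set of methods for continuous variables, and SPPB is one of them. The point is that a better method than the stated one is available, not that detail is missing.

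Second, the unpaired t test and the Mann-Whitney test are valid in a 1:1 randomised trial. This stands. Chance baseline imbalance is already reflected in their standard error and type I error, so it is a matter of precision and not of bias.

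Third, the wording permits an unpaired test on change from baseline, which does use the baseline score. This also stands, and at r = 0.7 it narrows the gain considerably.

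Fourth, the paired option may be meant only for description. Nothing in the article says that efficacy will be judged within arms, so misreading is a risk and not a plan.

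A reader might also infer that adjustment would recover most of the missing power. The documents do not support that. They give no r, and at r = 0.3 power rises by only 4 points at either alpha. The low starting figure of 39% also uses the larger SD and alpha 0.01, whereas Data Analysis tests at 0.05, where the start is 64%.

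**Conclusion.** The point holds as an improvement in precision and clarity. The article names only unadjusted between-arm tests or within-arm tests for continuous outcomes, SPPB among them, although a pre-intervention measurement is implied. A baseline-adjusted comparison would be more precise to the extent that baseline and follow-up SPPB are correlated.

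For r between 0.3 and 0.7 the gain over an unadjusted test on follow-up scores is 4 to 35 percentage points of power at alpha 0.01, and 4 to 26 at alpha 0.05 (SD 2.8, 44 per arm, difference 1.4). Only at the upper end of that range and at alpha 0.05 does power reach the stated 90%.

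The conclusion rests on baseline SPPB being collected, on a follow-up SD close to the baseline SD, and on the cited 3-month difference applying to this trial's time point. Adjustment does not repair the derivation of 44 per group or the disagreement between the design alpha of 0.01 and the analysis alpha of 0.05. Those need their own corrections.

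**What to change.** In Data Analysis, name one primary between-arm analysis for SPPB: a linear model of follow-up SPPB on treatment group and baseline SPPB, reporting the adjusted difference with its confidence interval whatever a normality test shows. Keep rank-based or bootstrap methods as sensitivity analyses, and restrict paired tests to description. Apply the same adjustment to other continuous outcomes that have a baseline value. If power is restated, give the assumed r and the power over a range of r.

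The model costs one degree of freedom and a change of wording, and needs no extra patients. Two things must be settled with it: the time point at which SPPB is the primary outcome, which the article leaves open, and an explicit entry for baseline SPPB in the assessment schedule, since at present it is only implied.

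### Minor: SF-36, psychological and nutritional measures have two follow-up visits each, but the only tests stated for continuous data omit patients missing at a visit; a repeated-measures model would use what they already gave

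*Protocol article*

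**What the plan says.** Outcomes names the primary outcomes (SPPB and 6-month all-cause rehospitalization), then the secondary ones, and only then adds: "In addition, we will evaluate the Short-Form 36-Item Health Survey (SF-36), psychological assessment, nutritional assessment and cardio-cerebrovascular events". The three measures discussed here therefore rank below both tiers. Table 2 marks them as follows:

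| Measure | Baseline | 1 month | 3 months | 6 months |
|---|---|---|---|---|
| SF-36 | X | X | X | |
| Psychological assessment | X | | X | X |
| Nutritional assessment | X | X | | X |

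Data Analysis sorts variables by type. "Normally distributed continuous variables were presented as mean ± SD and evaluated with paired or unpaired" Student's t test is the rule for normal data. Non-normal data are "determined by Wilcoxon signed-rank test or Mann-Whitney U test". Categorical data go to χ² or Fisher tests. The paragraph mentions no visit, no individual outcome and no repeated-measures model. Significance is two-sided at 0.05.

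On loss, Sample Size says: "Taking approximate a 20% drop-off rate and a 7% missing rate into account, the final sample size was set to 60 per group".

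**The concern.** An unpaired t or Mann-Whitney test takes one value per patient. If it is used to compare the arms on SF-36 at 3 months, a patient who gave baseline and 1-month scores and was then lost contributes nothing. The comparison is made among those who stayed. After an admission to cardiac intensive care with heart failure, loss related to health is plausible. If it is related to earlier scores in a different way in the two arms, the arms are no longer comparable at the later visit, although the earlier scores that could correct much of this are already in the database.

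What is at stake is limited. The Discussion lists improved quality of life among the matters not yet clarified, and SF-36 is the quality-of-life instrument scheduled. The trial's stated hypotheses, however, concern physical function, rehospitalization and mortality, and none of those rests on these three measures.

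**Working it through.** **Inputs from the article.** 60 per arm; allowance of 20% drop-off and 7% missing; two follow-up visits per measure; two-sided 0.05.

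**The plan's own figure.** 44 per group inflated for loss: 44/(1 − 0.27) = 60.3, or 44/(0.80 × 0.93) = 59.1. Both agree with the stated 60. In reverse, a single-visit test would have 60 × 0.80 = 48 per arm after drop-off alone, or 60 × 0.73 = 43.8, about 44, after both losses.

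**Assumptions not in the article.** Three normal measurements (baseline, first and second follow-up), each with SD 1; equal correlation ρ of 0.5 to 0.7 between visits; about 20% lost after the first follow-up visit. Two estimates of the arm difference at the second visit are compared: the difference in means among those seen (what the t test uses), and a likelihood-type estimate that predicts the second visit from baseline and the first visit within each arm.

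**1. Loss follows the first-visit score in controls only** (odds of loss × 2.7 per SD worse), random in the CR arm, no true effect, 4,000 simulated trials per setting:

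| ρ | Bias, t test (SD) | False positives | Bias, likelihood estimate (SD) |
|---|---|---|---|
| 0.5 | −0.091 | 7.4% | −0.001 |
| 0.6 | −0.108 | 8.7% | 0.003 |
| 0.7 | −0.128 | 9.3% | 0.000 |

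The sign is against CR: the worse controls leave, so the remaining controls look better. This case is adverse but not an upper bound. A steeper dependence in controls (1.5 instead of 1 on the log-odds scale; loss 24% in controls and 16% in CR) turned a true 0.40 SD at ρ = 0.6 into 0.24 by the t test, against 0.40 by the likelihood estimate.

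**2. The same first-visit rule in both arms.** With no true effect the bias is zero by symmetry. With a true 0.4 SD effect the t-test estimate is about 0.37 at ρ = 0.6, and the shortfall is about 0.02 to 0.03 SD over the range of ρ. The likelihood estimate is 0.40.

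**3. Loss depends on baseline, same rule in both arms.** Both estimates are 0.40 for a true 0.40.

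**4. Random loss.** Neither is biased. The standard error of the t-test estimate is √(2/48) = 0.204 SD. That of the likelihood estimate is √{2[(1 − R²)/48 + R²/60]}, with R² = 2ρ²/(1 + ρ). At ρ = 0.6, R² = 0.72/1.6 = 0.45, so the variance is 2(0.55/48 + 0.45/60) = 0.0379 and the standard error 0.195. The t test's is 0.204/0.195 = 1.05 times as large. Simulated values over the range of ρ were 0.201 to 0.205 against 0.192 to 0.196.

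**5. Loss depends on the unseen second-visit score.** For a true 0.40 the t test gives 0.35 and the likelihood estimate 0.37. Both are biased.

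**The case against.** The best defence is that Data Analysis is a short generic paragraph in a condensed article. It does not name SF-36 or the other two measures, and a longitudinal model or rules for missing data may well sit in a full protocol or analysis plan that is not shown. This stands in part: visit-by-visit testing is inferred, and the absence of a missing-data rule is no finding. But the article is not silent on method. It assigns continuous variables to t and rank tests, and neither can use a patient's earlier visits when the visit compared is missing. The point is about that stated choice.

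Three further objections stand in full:

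- The 20% is an allowance in a sample size built on SPPB. It is not a loss rate for SF-36 between 1 and 3 months, and placing all of it there is an assumption.
- Nothing in the article shows that loss will differ by arm.
- The article does not say that the psychological and nutritional assessments are analysed as continuous scores. PHQ-9 and GAD-7 are named under Intervention for assessment before the programme; the nutritional instrument is not named.

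A reader might infer that the quality-of-life comparison will be biased, or that a single-visit test is valid only if loss is unrelated to earlier scores. The documents support neither. Loss may depend on earlier scores by the same rule in both arms and leave the null comparison unbiased, as case 2 shows.

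**Conclusion.** The point holds as a cheap improvement of minor severity. For three additional outcomes, the stated tests discard data already collected on patients who miss a later visit. The consequence runs from a standard error a few percent larger (random loss), through 0.02 to 0.03 SD with a 0.4 SD effect (same rule in both arms), to about 0.09 to 0.13 SD and 7 to 9% false positives (loss tied to earlier scores in one arm only). Every one of these sizes rests on assumed correlations, an assumed 20% loss after the first follow-up visit and an assumed loss mechanism. The largest should not be read as the expected error. The primary and secondary conclusions are not affected.

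**What to change.** In Data Analysis, for SF-36 and for any psychological or nutritional measure scored on a continuous scale, replace the t and rank tests with one linear mixed model for repeated measures per outcome: arm, visit, arm × visit, baseline included (as a covariate or as a response), all available visits, unstructured covariance. Report the between-arm difference at each scheduled visit. Report deaths by arm alongside, and do not treat scores after death as ordinary missing data.

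The cost is one paragraph and a little programming. No new data, patients or software are needed, since SPSS 25 fits the model. The downside is that it relies on data being missing at random: it remains biased if loss depends on unseen scores (case 5), and it gains little for patients with no follow-up visit beyond what baseline provides.
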